#### Blinding and Allocation Concealment

Timing of treatment will be concealed to the therapists and to the examiners. Two separate masked therapists will perform the dental or the nutritional interventions. All laboratory assessments will be performed blindly.

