#### Brief Nutrition Education

The nutrition education will be conducted based on the health Belief Model (HBM) (28) addressing perceived susceptibility and severity of lacking the targeted behavior, perceived benefits and barriers of carrying out the targeted behavior, cues to action, and self-efficacy. With behavioral goals being increasing an individual's likelihood of food intake regarding fresh vegetables, fresh fruits, and high-quality protein foods (i.e., poultry, meat and aquatic product), the nutrition education session has been designed to be culturally tailored.

Participants will receive a 20-min coordinated nutrition education in the form of a slideshow presentation by a nutritionist in the clinical setting. On completion they will receive a copy of a pamphlet prepared in three parts (overall dietary goal, recipe examples mainly composed of softer and easy-to-chew food, and recipe examples composed of various food without restriction on the texture). The advice has been compiled with reference to the 4th edition of Dietary Guidelines for Chinese Elderly Residents (2016) by the Chinese Nutrition Society (29) that will be given to the participant separately. If a participant does not prepare his or her own meals, the person who does the cooking receives the dietary advice as well. A dietary checklist aiming to evaluate the compliance will be delivered with the pamphlet and patients will send it back after 1-week's recording.

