#### Food and Nutrient Intake

The primary outcome measure will be changes in intake of fresh fruits and fresh vegetables measured at 4 months using the 24-h dietary recall method. Protein% of total energy will also be calculated. Three 24-h dietary recall will be conducted through face-to-face interview, twice on weekdays and once on weekend. The data on food consumption will be converted into the corresponding nutrient contents based on the 6th version of China Food Composition Tables Standard Edition. Moreover, a modified simplified food-frequency questionnaire (FFQ) of 33 food group items (30) will be conducted at baseline, 4, 8, 12, and 16 months.

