##### Plasma Nutrient Biomarkers

Nutrient biomarkers will be assessed at baseline, 4, 8, 12, and 16-month follow-up by an accredited laboratory according to international standards.

a) Plasma vitamins A, B2, B12, folate, C and E will be measured by liquid chromatography-mass spectrometry (LS-MS).b) Plasma carotenoids (α- and β-carotene, β-cryptoxanthin, lycopene, lutein/zeaxanthin) and tocopherols (α- and γ) will be measured by LS-MS.

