### Data Quality and Assurance

All investigators involved in this study will be trained appropriately for the standard operating procedures including the questionnaire conduction, blood sampling and preservation, presurgical examinations and treatment (regarding periodontal diseases, caries, missing teeth and soft tissue disorders) and delivery of interventions.

(1) The 24-h dietary recall will be conducted by clinical nutrition specialists trained appropriately for the standardized interviewing procedures and assessment of dietary intake. The inter- and intra-examiner reliability with respect to the measurement of fresh foods and fresh vegetables intake will be assessed by the intraclass correlation coefficient (ICC). In order to ensure optimal inter- and intra-examiner reliability, ICCs needs to be more than 0.75.(2) The therapists, who will deliver the dental intervention, will be experienced specialists in implant dentistry fulfilling the Shanghai requirements. Treatment will be provided to the satisfaction of the clinician and patient. For logistic reasons, five therapists will be included in this study.(3) The investigator who performs dietary interventions will be trained in delivering a standardized dietary instruction session including the verbal instruction and demonstration of the pamphlet. In addition, the investigator will be trained in the use of questionnaires.

Regular monitoring for assuring protocol compliance, and data quality at the clinical site, including review of source documents and records, consent forms, etc will be performed by an investigator trained in both GCP and the specific procedures. Furthermore, the clinical research coordinator will audit the case report forms for the first few patients to ensure correct filling of forms. The study will also be monitored by the compliance office of the National Clinical Research Center of Oral Diseases and Clinical Research Center of the 9th People's Hospital.

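### The stated masking of therapists and examiners cannot hold for the dental factor, and the self-reported primary outcome has no objective check assigned to it

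*Protocol article*

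**What the plan says.** All references are to the protocol article.

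- **Masking.** Blinding and Allocation Concealment states "Timing of treatment will be concealed to the therapists and to the examiners". It continues "Two separate masked therapists will perform the dental or the nutritional interventions" and "All laboratory assessments will be performed blindly". No masking of participants is claimed.
- **Primary outcome.** The section on Food and Nutrient Intake defines it as follows: "The primary outcome measure will be changes in intake of fresh fruits and fresh vegetables measured at 4 months using the 24-h dietary recall method". On how it is collected: "Three 24-h dietary recall will be conducted through face-to-face interview".
- **Who collects it.** Data Quality and Assurance, item 1, gives the recall to trained clinical nutrition specialists. Item 3 covers the person who delivers the dietary session and adds "In addition, the investigator will be trained in the use of questionnaires", without naming the questionnaires.
- **Education content.** Brief Nutrition Education has a nutritionist deliver the session, "With behavioral goals being increasing an individual's likelihood of food intake regarding fresh vegetables, fresh fruits". Participants also take home a pamphlet with dietary goals and a one-week checklist.
- **Objective markers.** Plasma Nutrient Biomarkers lists vitamin C and carotenoids among the analytes that "will be measured by liquid chromatography-mass spectrometry", at baseline, 4 months and later visits.

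**The concern.** The article asserts concealment from the people who treat and assess, yet its own procedures reveal half of the factorial allocation to anyone facing the participant. That matters most for the primary outcome, because intake is reported in conversation. An interviewer who can see that a participant has a new fixed prosthesis may probe or record differently, which bears on the dental contrast.

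A second source of bias would remain even with perfect examiner masking. Participants in A and C have been told which foods to eat more of and are then asked how much of those foods they ate. That bears on the dietary and combination contrasts, in the direction the trial hypothesises. The two sources need separate remedies: an accurate masking statement with separated roles for the first, and a measure that does not depend on self-report for the second.

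**Working it through.** **Step 1. Can the dental factor be concealed at 4 months?**

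| Section | What it implies at the 4-month visit |
|---|---|
| Study Overview | A and B have had the dental intervention; C and D are still waiting |
| Dental Intervention | Remaining teeth are extracted and a fixed interim full-arch restoration is fitted within a day of surgery |
| Table 1; Peri-Implant Soft and Hard Tissue Health | Peri-implant probing at 4 months, possible only in people who have implants |
| Food and Nutrient Intake | The recall interviewer sits opposite the participant |
| Treatment of Trial Participants | The dietary session is adapted to dental status, so the person giving it must know that status |

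The presence or absence of the prosthesis is itself the timing of dental treatment. The examiner who probes implants and the person who gives the dietary session cannot be unaware of it, and a face-to-face interviewer can readily see or hear it.

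**Step 2. Can the dietary factor be concealed?** The session lasts 20 minutes and leaves no visible sign. A separate interviewer could stay unaware unless the participant mentions it. The condition is that the interviewer is not the person who gave the session. The text separates the dental therapist from the nutrition therapist, but does not say that either is separate from the outcome interviewers.

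**Step 3. What checks the self-report?** The Discussion acknowledges the recall's limits and offers the food-frequency questionnaire, which is also self-report. Vitamin C and carotenoids are assayed blind at the same visits, but the article does not link them to the recall.

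**Step 4. How much could over-reporting matter?**

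Inputs from Sample Size: SD 200 g/day; increases of 50 g (dental), 70 g (dietary) and 245 g (both); alpha 0.05; 80% power; 20% loss; 30 per group, so 30 × 0.8 = 24 evaluable. Assumptions: zero change in group D, and a two-sided test.

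*The plan's own figure first.*
- Dental main effect: (245 + 50)/2 − (70 + 0)/2 = 112.5 g.
- n per margin = 2(1.96 + 0.84)² × 200²/112.5² ≈ 50, or 25 per group. Inflation gives 25/0.8 = 32 (rounded up), or 25 × 1.2 = 30. The stated 30 is reproduced to within 2.
- SE of a main effect at 24 per group: 200 × √(2/48) = 40.8 g.
- Dental power: Φ(112.5/40.8 − 1.96) = 78.7%.
- Dietary main effect: (245 + 70)/2 − (50 + 0)/2 = 132.5 g, with power 90.1%.

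*Sensitivity.* Suppose education has no true effect and A and C over-report by b g/day relative to B and D. The rejection rate is Φ(b/40.8 − 1.96) + Φ(−b/40.8 − 1.96).

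| Assumed b (g/day) | False-positive rate, dietary main effect |
|---|---|
| 0 | 5% |
| 10 | 5.7% |
| 20 | 7.8% |
| 30 | 11.4% |
| 50 | 23.2% |
| 70 | 40.3% |

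For scale, 70 g is the whole assumed effect of advice alone and 70/132.5 = 53% of the planned dietary main effect; 10 g is 10/132.5 = 8% of it.

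This takes Study Overview at its word that A and C are educated before the 4-month recall. Table 1, as extracted, appears to place their dietary session in the 4-month column. That may be an extraction fault; if not, the two places must be reconciled.

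**The case against.** The strongest reply has four parts.

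1. **Role separation is implied.** The recall is assigned to clinical nutrition specialists, and the masking section names therapists and examiners as different groups. A reader might infer from the line on questionnaire training that the person who gives the dietary session also collects the primary outcome. The documents do not say so: the questionnaires are unnamed and the recall is never called one. What stands is that nothing excludes the overlap, and masking to the dietary factor depends on excluding it.
2. **The claim concerns timing, and masking can partly work.** A reader might infer that examiner masking is impossible altogether. It is not: a separate interviewer can be kept unaware of the dietary factor. For the dental factor the narrower wording does not help, because prosthesis status at 4 months reveals the timing.
3. **The number and the masking flaw concern different biases.** This is correct. The sensitivity table describes over-reporting by participants in the educated arms, which better examiner masking would not remove. No figure is available for what a visible prosthesis does to the dental contrast. The range of b is an assumption, and its low end is almost harmless.
4. **The trial already has safeguards.** It uses three recall days, standardised interviewing, an intraclass correlation above 0.75, and blind-assayed markers. A reader might infer that an artefact could never be told from a real change; the markers mean that is too strong. But examiner agreement does not detect a participant's own over-reporting, and the markers help only if their role is fixed beforehand.

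Outcome hierarchy is often left to an analysis plan that is not shown. The masking statement is different: it is in the current text and is wrong for one of the two factors.

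**Conclusion.** The point holds for the dental factor on the article's own procedures, with no outside assumption. Therapist and examiner masking to that factor should not be claimed. For the dietary factor, masking is attainable but not secured. The self-reported primary outcome is exposed to participant reporting bias, and the only stated check shares that weakness.

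The size is conditional. With SD 200 g, 24 evaluable per group and an assumed 10 to 70 g/day of differential over-reporting, the dietary main effect's false-positive rate would be about 6% to 40% instead of 5%. The documents neither support nor exclude any value in that range. The sample size is unaffected. This should be corrected because it governs what the trial may say about its own masking and how firmly it may conclude that diet changed.

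**What to change.** 1. **Restate the masking section.** Do not claim that therapists or examiners are masked to dental status. Limit interviewer masking to the dietary factor. Keep the statement that laboratory work is blind. Say plainly that participants are not masked.
2. **Separate the roles.** State that staff who deliver the dietary session do not conduct the 24-h recalls or administer the food-frequency questionnaire.
3. **Give the markers a defined role.** Name the 4-month change in plasma vitamin C and carotenoids as a prespecified supportive outcome in the same factorial analysis as the primary outcome. They corroborate direction only: they do not measure grams per day, cannot correct the primary estimate, and should not be a condition for success. If they do not agree with the recall, report the self-report limitation alongside the primary result.

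**Cost.** There are no new assays, visits or participants. The downsides are a minor constraint on task assignment and a less favourable, but accurate, masking statement.

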#### Removal and Withdrawal Criteria

Those who have been selected for this trial and fall into one of the following circumstances are regarded as removed cases.

(1) Violation of important entry criteria;(2) Receiving no study interventions;

Each participant has the right to withdraw from the study at any time. In addition, the investigators may discontinue a participant from the study at any time if the investigators consider it necessary for any reason including:

(1) Best interest of the patient.(2) Ineligibility (either arising during the study or retrospective having been overlooked at screening).(3) Significant protocol deviation.(4) Significant non-compliance with treatment regimen or study requirements.(5) An adverse event which requires discontinuation of the study or results in inability to continue to comply with study procedures.(6) Inability to continue to comply with study procedures (e.g., moving to another city).(7) Consent withdrawal.(8) Loss to follow up.

If any subjects withdrawn from the study, no particular observation or treatment would need to continue. Subjects would be replaced if anyone withdrawn after the study started.

Regardless of the reason, complete clinical data should be retained for subjects who withdraw from the trial. The reason for withdrawal or early termination will be recorded in the CRF (case report form). If the participant is withdrawn due to an adverse event, if any, the investigator will arrange for follow-up visits until the adverse event has resolved or stabilized.

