#### Study Overview

The study is designed as a factorial randomized controlled clinical trial testing the benefits of dental and/or dietary interventions on changes in fresh fruits and fresh vegetables intake at 4 months (Table 1). Group A (DE+/DI+) will receive the full treatment regimen. Group B (DE+/DI–) will receive implant-supported fixed prosthesis at first and nutrition education after a 4-month waiting period. Group C (DE–/DI+) will receive the nutrition education at first and implant treatment after a 4-month waiting period. Group D (DE–/DI–) will receive the same treatment as Group A after a 4-month waiting period (Figure 1). The waiting period is equal to the current waiting list in the department. Subjects will be followed for an additional 12-month period. All procedures will follow the principles of the Declaration of Helsinki on experimentation involving human subjects, all subjects will provide written informed consent. The trial has been approved by the Institutional Review Board of the Shanghai Ninth People's Hospital, Shanghai Jiao Tong University School of Medicine (Approval No. SH9H-2021-T321-3) and is registered in ClinicalTrials.gov (NCT05334407). The trial will be independently monitored by the office of clinical research of the Shanghai Ninth People's Hospital. Any modifications to the protocol with impact on the conduct of the study will require a formal amendment to the protocol. The SPIRIT summary of the trial procedures is illustrated in Supplementary Table 1.

**Table 1 T1:** Overview of the schedule of enrolment, interventions, and assessments.

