## Data Analysis

### Sample Size

The sample size has been determined based on the primary outcome: changes in the intake of fresh fruits and fresh vegetables. Based on the relevant studies where the average fruit and vegetable intake was about 255 ± 200 g per day in edentulous elderly (17), we assume that the average fruit and vegetable intake will increase 50 g, 70 g and 245 g in patients receiving dental prostheses alone, brief dietary advice alone, or the combination dental treatment with brief dietary advice, respectively. With an anticipated 20% loss to follow-up, 30 patients are needed in each group to test the significance of dental treatment, brief dietary advice, alone or in combination with alpha set at 0.05 and with 80% power. Due to limitations in the baseline knowledge for precise sample size calculations and the efforts required for an adequate pilot study, adaptive adjustment of sample size will be performed. Sample size calculation will be re-estimated after obtaining the primary outcome of 10 patients in each group. Based on the interim analysis for adaptive design, several scenarios have been identified: (i) the original sample size estimation is appropriate and the study will be completed accordingly; (ii) the original sample size will be insufficient but will still be within the capability of recruitment of the study center, in such case the sample size will be expanded according to the adaptive design principles; (iii) the original sample size will be insufficient but too large for successful completion of the study at the study center alone, in such scenario the study will be completed as a pilot study with the original sample size and a multicenter trial will be designed and implemented based on the results.

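### Withdrawn participants need not be observed and are replaced, which selects the 4-month groups after randomisation; the no-intervention removal ground is unworkable for Group D

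*Protocol article*

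**What the plan says.** The section Removal and Withdrawal Criteria sets up two categories.

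- **Removed cases.** Those selected for the trial who "fall into one of the following circumstances are regarded as removed cases". There are two grounds: violation of important entry criteria, and "Receiving no study interventions".
- **Withdrawn participants.** Participants may leave at any time, and investigators may discontinue them for any reason they think necessary. The listed reasons include protocol deviation, loss to follow-up and "Significant non-compliance with treatment regimen or study requirements".

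For withdrawn participants the section says that "no particular observation or treatment would need to continue", and then: "Subjects would be replaced if anyone withdrawn after the study started". It also says that "complete clinical data should be retained for subjects who withdraw from the trial", and that withdrawals for an adverse event are followed until the event resolves or stabilises.

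Three other places bear on this.

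- Study Overview: Group D "will receive the same treatment as Group A after a 4-month waiting period".
- Table 1: the 24-h dietary recall, which carries the primary outcome, is scheduled at enrolment and at 4 months only.
- Sample Size: 30 per group are planned "With an anticipated 20% loss to follow-up".

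**The concern.** The comparison at 4 months is protected by randomisation only if the people compared are the people randomised. Three features of the rule work against that.

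1. **Withdrawal can depend on arm and on response.** The nutrition education comes with a one-week checklist meant to evaluate compliance (Brief Nutrition Education). As the Study Overview describes the arms, only Groups A and C receive it before month 4. Failing to follow dietary advice is partly a result of giving that advice, so withdrawing people for it selects on response.
2. **The primary outcome can be lost for good.** With one post-baseline recall time point and no duty to keep observing, a withdrawal before month 4 leaves no primary measurement. No later analysis plan can restore data that were not collected.
3. **Newcomers fill the gap.** Replacement makes the number of completers look as planned, while those who stopped are represented by people who did not. The sample-size re-estimation after 10 patients per group would draw on the same selected data.

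The no-intervention removal ground is a further problem. Taken at its word, it describes every Group D participant at the primary endpoint.

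**Working it through.** **1. The plan's own sample size.** Inputs from Sample Size: SD 200 g; increases of 50 g (dental alone), 70 g (diet alone) and 245 g (both); alpha 0.05; power 80%; 20% loss. My assumptions: no change in Group D, a two-sided test, and SD 200 applied to the change.

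- Dental main effect = (50 + 245)/2 − (0 + 70)/2 = 147.5 − 35 = 112.5 g.
- n per margin = 2 × (1.96 + 0.84)² × 200² / 112.5², which gives 50, or 25 per cell.
- With loss: 25 × 1.2 = 30, the stated figure. Dividing instead, 25/0.8 = 31.25, or 32.
- Diet main effect = (70 + 245)/2 − (0 + 50)/2 = 157.5 − 25 = 132.5 g, which needs 18 per cell, or 18/0.8 = 22.5, so 23 with loss.

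So 30 per group is consistent with the factorial main effects after an allowance for loss.

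**2. Is replacement needed?** With no replacement and 20% loss, 30 × 0.8 = 24 per cell remain (a derived figure; the document does not state it). Power is then 78.7% for the dental main effect and 90.1% for the diet main effect, close to or above the planned 80%. Replacement at 20% loss would add 120 × 0.2 = 24 people in one round, or 120/0.8 − 120 = 30 to reach 120 completers. Dental power would rise to 86.9% at 30 completers per cell, but in a selected set.

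**3. Illustration of the size.** The document gives no withdrawal rate for non-compliance, so I assume a share p of 10–20% of an arm. I also assume that all of them are withdrawn, and that each is replaced by someone with the mean gain of the compliers. If non-compliers gain g, the true arm effect E is (1 − p) × c + p × g, so the effect seen after replacement is c = (E − p × g)/(1 − p).

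| Effect | g assumed | p = 10% | p = 20% |
|---|---|---|---|
| Diet alone, E = 70 g | 0 g | 70/0.9 = 78 g | 70/0.8 = 87.5 g |
| Both, E = 245 g | 50 g (the plan's dental-alone gain) | (245 − 5)/0.9 = 267 g | (245 − 10)/0.8 = 294 g |

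The overstatement is 11–25% for diet alone (77.8/70 and 87.5/70) and about 9–20% for the combination (266.7/245 and 293.75/245).

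**4. Group D, by reading.** The primary outcome is measured at 4 months, and Group D starts treatment only after the 4-month wait. Any Group D participant who leaves while waiting therefore meets the no-intervention ground. A Group A participant who leaves after surgery does not. What follows depends on what being a removed case means for the analysis, which the document does not say. Neither the size nor the direction of any resulting shift in Group D can be computed.

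**The case against.** The strongest reply is that the section says less than it first appears to. Several readings are tempting, and the text does not carry them.

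- *Never-treated participants are also replaced and no longer observed.* The text does not say so. Removed and withdrawn are separate categories, and the observation and replacement sentences concern the withdrawn.
- *Observation must stop.* The wording permits stopping and does not require it. Adverse-event withdrawals are followed and data are retained. This stands, but safety visits and retained earlier data do not provide a 4-month recall that nobody is obliged to take.
- *The rule falls hardest on the waiting arm.* A Group A leaver is also withdrawn and replaced, so on those two points the arms are treated alike. The asymmetry bites only if removed cases are left out of the analysis, which is not stated and may be settled in an analysis plan not shown here.
- *Replacement contradicts the 20% allowance.* It does not. The two can coexist; the second is redundant.
- *The combined effect would be inflated to 272–306 g.* That sets the gain of Group A's diet non-compliers to zero and ignores the 50 g that the plan assigns to dental treatment alone.
- *Up to 24 of 120 are affected.* People lost to follow-up lack 4-month data whatever the rule says, so the loss allowance does not measure the rule's effect.

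It is also fair to say that investigators may, and need not, withdraw non-compliers, that the dietary intervention is a single 20-minute session, and that analysis populations are commonly left to the analysis plan. These points limit how large the effect may be. They do not remove the stated replacement rule or the absence of a duty to collect the primary outcome after discontinuation.

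**Conclusion.** The concern holds as a fault in a stated rule. Following the section as written can lose the primary outcome selectively, by compliance and so by arm, and fills the places with people selected after randomisation. The no-intervention ground cannot be applied sensibly to Group D at the primary endpoint. A heavier effect on that arm is conditional on removed cases being excluded from analysis.

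The actual bias is not computable from the document. The 78–88 g and 267–294 g figures are illustrations. They rest on 10–20% of an arm being withdrawn for non-compliance, on their gaining 0 g (diet alone) or 50 g (combination), and on replacement by typical compliers. The finding that replacement is not needed rests on the main-effect reconstruction, with power of 78.7% and 90.1% at 24 per cell.

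**What to change.** Amend the protocol as follows.

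1. Delete the sentence on replacing withdrawn subjects, and delete receipt of no intervention as a ground for removal.
2. State that participants who stop or do not comply with treatment stay in the study for data collection, and that their 4-month 24-h recalls are taken unless they withdraw consent to data collection. This leaves decisions on stopping treatment as they are.
3. State that all randomised participants are analysed in their assigned group, with any compliant-only set as a sensitivity analysis.
4. Keep the 20% inflation as the only allowance for loss.

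Cost: one amendment, and up to three face-to-face recalls (two weekdays and one weekend day, per Food and Nutrient Intake) for each discontinued participant who still consents. If discontinuations equalled the whole 20% allowance and all could be interviewed, that would be 24 × 3 = 72 interviews. The number would be lower in so far as the allowance is used up by people lost to follow-up, who cannot be interviewed.
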